## 14.2 Study Activation

Following ethical review and approval, study sites submitted all required administrative documentation (see Section 15.1) to UCSF. A comprehensive study training took place when data collection forms were close to final. After the training, final adjustments were made to the SOPs, forms, translations and back-translations. The trial was initiated at each study site independently when the co-PI of that study site and UCSF agreed that all systems were in place.

## Study Monitoring and Independent Audits

UCSF, as the sponsor and overall coordinator of this trial, is responsible for ensuring the proper conduct of the trial. UCSF designates monitoring and quality control staff for the trial. Part of this responsibility is shared with Ibis Reproductive Health staff.

Monitoring is separated into two categories: general monitoring and clinical monitoring. QC procedures for laboratory testing are described in Section 10.3. In addition to the monitoring procedures outlined below, UCSF and Ibis arrange for independent audits of the trial, including laboratory audits. Quintiles Transnational Corporation conducted a complete external audit of each MIRA study site in October-November 2005. Quintiles produced final reports that were addressed by the sites, Ibis and UCSF. Responses to audit findings were submitted to Quintiles.

General monitoring is conducted by our monitors who travel regularly to the three trial sites according to a pre-determined monitoring schedule. The monitoring coordinator trains the monitors and checks their work periodically throughout the trial.

The monitors’ duties are:

- To verify compliance with protection of human subjects and other research regulations and guidelines
- To assess adherence to the study protocol and GCP guidelines
- To confirm the quality and accuracy of information collected at the study site and entered into databases

Study site investigators and staff allow study monitors to inspect study facilities and documentation and to observe the performance of study procedures. As part of the monitoring process, study participants are asked to acknowledge the possibility that a representative of UCSF may request an interview. If an interview is requested, the study participant has the option of accepting or declining the interview. Monitors verify that written informed consent is being obtained from participants, that all information is being kept confidential, that regulatory files are up to date, and that AEs and SAEs are properly documented and reported. They ensure that participants enrolled in the trial are indeed eligible, that follow up is occurring according to protocol, and that reported data are accurate and complete. They inspect storage and inventory of diaphragms and other study supplies to ensure proper accountability. During the monitoring visit, the monitors document all actions they take. After the monitoring visit, they write a monitoring report, which is distributed to the Monitoring Coordinator, Protocol Director, Project Director, Data Manager, and to all co-PIs. The study site will maintain a monitoring log to document all monitoring visits.

Monitoring of clinical procedures is conducted in conjunction with the Medical Advisor on this trial. The Medical Advisor trains or helps develop training curriculum for the study clinicians prior to trial initiation and develops and reviews clinical operating procedures. Periodic monitoring of clinical procedures is conducted throughout the trial, including direct observation of clinical procedures. After monitoring visits, the monitor distributes a report as outlined above.

## Protocol Amendments and Deviations

Changes to the protocol are made only when written protocol amendments signed by the co-PIs have been approved by the relevant IRBs. Protocol amendments may affect consent forms for current and future patients, which have to be modified accordingly and approved by the relevant IRBs.

If a protocol deviation is required to protect the life or physical well being of a participant in an emergency, it may be carried out without prior approval from UCSF or relevant IRBs. The study site co-PI or designee must, however, report the deviation to UCSF co-PI, protocol director and Project Director as soon as possible and no later than five working days after the emergency comes to the attention of the study staff. They also keep a record of all such deviations, which documents the dates of and reasons for each deviation, and report them to the local IRB. The UCSF Project Director notifies the UCSF IRB according to IRB guidelines.

Other deviations from the protocol may not be carried out without prior approval from UCSF and possibly the relevant IRBs when the change involves the rights, safety or welfare of participants. If an inadvertent protocol deviation or incident (unanticipated problem) has occurred, the site investigator or designee reports it to the UCSF Project Director and/or Protocol Director within 5 working days of becoming aware of the event. The UCSF IRB requires that all major violations be reported from all MIRA sites. Major protocol violations are defined as any unapproved changes in the research study design and/or procedures that are within the investigator’s control and not in accordance with the approved protocol that may affect the participant’s rights, safety or well-being, or the completeness, accuracy and reliability of the study data.

## Use of Information, Publishing, and Ancillary Studies

No presentations or publications about any data collected during this trial may be made without the joint approval of all co-PIs. Writing and publication of the main publications, which address the primary and secondary trial objectives outlined in this protocol, will be a joint process between investigators at UCSF, Ibis Reproductive Health, the University of Zimbabwe, the Medical Research Council, and the Perinatal HIV Research Unit. The co-PIs will jointly determine the appropriate manuscript writing, review and publication process for the main publications as well as additional publications that are directly related to the trial.

Ancillary studies are defined as studies that do not address the primary and secondary objectives of the trial, but directly involve trial participants, trial site resources reserved for the trial, and specimens or data collected during the trial as described in this protocol. Examples of ancillary studies include surveys or qualitative research with trial participants, the testing of stored specimens, the addition of specimens or lab tests to the ones described in this protocol, and secondary data analysis of trial data. Proposals for all such studies should be reviewed and approved by the four co-PIs as well as relevant IRBs if applicable before they can be implemented. UCSF reserves the right to overrule decisions made by the co-PIs if deemed necessary to avoid jeopardizing the primary and secondary objectives of the trial.

**A. Introduction**

Bacterial vaginosis, the most common bacterial genital infection in women of reproductive age has been linked to considerable gynecologic and obstetric morbidity. Recent studies demonstrate that BV may be a cofactor in acquisition of human immunodeficiency virus type (HIV) infection. 1-3. The highest prevalence of BV has been in sub-Saharan Africa where HIV infection is also common 2,3. It has been postulated that BV may increase susceptibility to HIV infection by a variety of mechanisms including possibly altering the host’s defense system through the absence of the normal H2O2-producing vaginal lactobacillus (which allow to maintain the natural acidic pH of the vagina), with loss of the protective myeloperoxidase halide-hydrogen peroxide system 4, and by production of metabolic by-products that may increase HIV replication 5,6 or activate target cells for HIV infection 7. If any of these hypotheses are correct, reduction of BV prevalence could significantly reduce female HIV acquisition. The high prevalence of BV in sub-Saharan Africa remains unexplained. Though considerable evidence supports sexual transmission of BV, factors like clothing, climate and hygiene may influence vaginal flora. Of the various risk factors associated with BV, the contribution of each to causing BV may vary depending on hygienic, sexual and other practices 8. BV treatment with metronidazole was first found to be to be effective in the initial clearing of symptoms and signs of BV 9, but has since proven disappointing even in industrialized countries, since recurrence rates reach 40% within 3 to 6 months after treatment with oral or intravaginal medication 10,11.In Uganda, administration of metronidazole, azithromycin and ciprofloxacin to large populations of adults of reproductive age every 10-months did not reduce the prevalence of BV below 50% 12.

Use of the diaphragm with nonoxynol-9 (N9) based spermicide has been associated with altered vaginal bacterial microflora including decrease rates of lactobacillus colonization 11. However, most regard the alteration of vaginal flora and increased risk of urinary tract infection a direct result of the N-9 spermicide and not related to the diaphragm alone 12. Importantly, Buffergel a microbicide with the ability to maintain a low vaginal pH was associated with profound reductions in BV after a short period of use 13. Therefore, we propose to study the effect of the diaphragm used with Replens (a commercially available vaginal lubricant with pH buffering capacity) on the vaginal flora and on the rate of BV in women enrolled in a randomized controlled trial.

**B. The Specific Aims**

**Specific Aim 1:** To compare rates of BV in women in the diaphragm with Replens with those of women in the condom only arm.

- 1. To compare Nugent’s scores in the 2 arms as the full 10 point scoring system during a 12 – 24 month follow-up after randomization, and
  2. To assess the influence of the intervention on vaginal colonization by *Lactobacillus spp*. as note on Gram stain.

**Specific Aim 2:** To determine whether women in the diaphragm used with Replens arm have an altered rate of recurrence after treatment of BV compared to women in the condom only arm.

**C. Methods**

**C.1 Overview**

At the Zimbabwe site, self-collected vaginal swabs will be collected on the 500 women enrolled in the RCT at their enrollment visit and every three months per study protocol. Data on recent vaginal hygiene and other practices that may affect vaginal microflora will be collected on an additional questionnaire at every follow-up visit. Since the site will enroll over 2,000 women over the course of the randomized trial, enrollment for the BV component will take place at one of the three recruitment centers, and will be closed once the full sample size has been attained.

To study Aim II, 500 women with symptomatic BV will be required. Unfortunately, since we will not be able to perform vaginal Gram stains in real-time, the initial diagnosis of BV will be made using the modified Amsel’s criteria (pH > 4.7, positive whiff test and clue cells on wet mount). Those diagnosed with BV will receive a 5-day course of metronidazole 400 mg three times per day. Vaginal Gram stains will also be collected. Only women with a Nugent score  7 and with 3 of 3 Amsel’s criteria will be analyzed. Women enrolled in Aim II will have a vaginal Gram stain repeated on a self-collected vaginal swab three months after treatment. The prevalence of BV after three months will serve as the primary endpoint for this aim.

**C.2.1 Analysis of major study endpoints**

**C.2.1.1 Aim 1 major endpoints**

The primary endpoint will be based on Nugent criteria; BV free survival will be defined as Nugent score < 7. Data will be analyzed initially in an intent-to-treat manner comparing the percent of quarterly visits (on average women will undergo 6 follow-up visits) with BV for those assigned to the diaphragm/Replens arm vs. the condom only arm. A secondary analysis will be performed to compare women compliant with the diaphragm and Replens to the control arm.

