## Product Administration Plan

At enrollment, women randomized to the diaphragm group are fitted for diaphragm size and receive an Ortho All-Flexdiaphragm. Staff also instruct women about how to use the Replens gel and how to properly clean and store their diaphragms and gel applicators***.***

To improve diaphragm compliance during the trial, only women who are able to correctly insert the diaphragm are enrolled into the study. In order to avoid introducing a bias between the study arms, all women practice diaphragm insertion *before* they are randomized. Women who are not able to correctly insert/remove the diaphragm after five attempts are not eligible to enroll into the study. Following randomization, women in the diaphragm arm will receive condoms, a diaphragm and gel, and more counseling. Women in the condoms-only arm receive condoms and counseling and are told that they can receive a diaphragm to keep and use as they wish at the end of their participation in the study.

Throughout the study, we encourage women to return to the study site if they experience any problems using the diaphragm or would like further instructions or advice. We also ask women to return to the clinic or mobile site at any time during the study if they feel discomfort. A clinician provides a larger- or smaller-sized device as needed. Women who have a vaginal delivery during the study are re-fitted for diaphragm size. As part of ongoing quality assurance processes, there are systematic checks of diaphragm fittings, which sometimes result in a woman being fitted with a new diaphragm size. Replacements for damaged or lost diaphragms can be obtained in the clinic at any time during the study or can be distributed through home visits when compatible with confidentiality requirements.

Women are instructed to insert the diaphragm at any time before sex. We ask them to put lubricant gel in the dome and rim of the diaphragm at the time of insertion and to reapply gel in the vagina before each act of vaginal sex. We ask them not to cleanse the vagina or the diaphragm immediately after sex but to leave the device in place for at least 6 hours. Staff also instruct women about how to properly clean and store their diaphragm and gel applicator. Women are allowed to resume normal vaginal hygiene after sexual intercourse (*i.e.* cleanse outer genitalia with water or water and soap) as long as they do not remove the diaphragm within six hours after sex.

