## STI and RTI Diagnosis and Treatment

As described in Sections 9.3 and 9.4, we test all women who are eligible for the trial and choose to participate for HIV and other STIs. Women who are laboratory positive for *Chlamydia trachomatis* and/or *Neisseria gonorrhoeae* complete treatment before they are enrolled. Women who have a diagnosed or suspected current STI or reproductive tract infection at enrollment including laboratory diagnosed *Trichomonas vaginalis* and/or *Treponema pallidum* are provided treatment and enrolled. Throughout the study, we collect specimens for STI testing at each follow-up visit. We contact and inform infected women of their results. We provide them with STI treatment in accordance with WHO guidelines free of charge and offer STI testing and treatment for their partners. We pay special attention to possible urinary tract infections (UTIs) because of the association between such infections and diaphragm use.31,32 The study pays for the treatment of incident UTIs diagnosed during the study period.

For other medical conditions identified during study screening and/or follow-up procedures, we refer participants to other sources of care available in their communities. In certain cases of infections or epithelial lesions, the study clinician may decide to interrupt diaphragm and gel use.

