**C.2.2 Sample size determination, Data Management and statistical analysis**

**C.2.2.1 Aim 1 sample size**

Based on data from other studies conducted on BV in sub-Saharan Africa, we assume that 20% of women will have BV by Gram stain at baseline, and at every visit for those enrolled in the non-intervention condom only arm. We further assume that > 80% of BV will be asymptomatic, and therefore treatment with metronidazole will have a limited effect on the overall prevalence of BV at subsequent visits. The primary outcome will be visit-specific BV prevalence. We assume that outcomes will be compared between arms on an intent to treat basis using generalized estimating equation (GEE) logistic regression model controlling for a within-participant correlation between repeated outcomes of 0.2, and that annual rates of loss to follow-up will be 5%. Based on these assumptions, 250 women per arm should be sufficient to insure 80% power to detect a  25% difference in prevalence between the two study arms as significant at the 5% level (based on a two-sided test). This corresponds to a relative risk (odds ratio) of 0.75 (0.70).

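### BV sub-study Aim 1: the secondary analysis sets compliant diaphragm-arm women against the whole control arm, so selection after randomisation can produce an apparent effect in either direction

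*Protocol*

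**What the plan says.** Appendix 16.1, C.2.1.1, starts from the randomised comparison: "Data will be analyzed initially in an intent-to-treat manner comparing the percent of quarterly visits" with BV, by assigned arm. The same paragraph then fixes a second contrast: "A secondary analysis will be performed to compare women compliant with the diaphragm and Replens to the control arm". The appendix does not define compliance, applies no matching restriction to controls, and states no covariates for this contrast. C.2.2.2 restates only the intent-to-treat analysis, by GEE logistic regression.

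The main protocol deals with per-protocol analyses in 12.7 and 12.7.3. Section 12.7 accepts that they can be confounded and leaves the make-up of the per-protocol set to a data analysis plan. Section 12.7.3 lists covariates: frequency of product and condom use, and baseline factors that differ significantly between the randomised arms. Both sections are written for the HIV and STI endpoints.

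**The concern.** Randomisation makes the two whole arms comparable. It does not make the compliant part of one arm comparable with the whole of the other, which contains women who would have complied and women who would not. If the two kinds of women differ in BV risk for any reason (hygiene, sexual behaviour, condom use), the contrast mixes that difference with any product effect.

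The covariates in 12.7.3 would not repair this even if they were carried into the appendix. They are chosen because they differ between randomised arms, whereas the imbalance here arises within one arm, between compliers and non-compliers. The HPV appendix (16.2, Limitations) shows that the investigators know of the problem: it says diaphragm users may douche more and undertakes to control for such co-interventions. The BV appendix gives no such undertaking, although its endpoint is vaginal flora.

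At stake is a secondary result that could be reported as efficacy among users of the product when it reflects only who those users are.

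**Working it through.** **Inputs from the protocol.**
- Six visits per woman: "on average women will undergo 6 follow-up visits" (C.2.1.1).
- BV prevalence 20%: "we assume that 20% of women will have BV by Gram stain at baseline", and at every visit for controls (C.2.2.1).
- Correlation 0.2: "controlling for a within-participant correlation between repeated outcomes of 0.2" (C.2.2.1).
- 250 women per arm, two-sided 5%, 80% power, relative risk 0.75 (C.2.2.1).

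**Inputs assumed.** The documents give neither the compliant share for this sub-study nor BV by compliance.
- Compliant share c = 30%, 50%, 70%. The pilot study (3.4) reported consistent use by close to half, but in inconsistent condom users with a different gel over six months.
- Ratio r of BV prevalence, non-compliers to compliers = 1.25, 1.5, 2.0.

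**The plan's own figures.** A fall from 20% to 15% gives an odds ratio of (0.15/0.85)/(0.20/0.80) = 0.706, in line with the stated 0.70. The sample size does not reproduce under the stated two-sided test. It needs 906 independent observations per arm; with six visits, 906 × (1 + 5 × 0.2)/6 = 302 women per arm, against 250 stated. That is a separate matter, and nothing below depends on it.

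**Bias with no product effect.** Both arms have 20% BV overall, so compliers have prevalence 0.20/(c + (1 − c)r). The expected relative risk of compliers against all controls is

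RR = 1/(c + (1 − c)r).

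For c = 0.5 and r = 1.5: 1/(0.5 + 0.75) = 0.80, which is 16% against 20%.

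**Chance of a significant protective result.** Each setting had 4,000 simulated trials, with beta-binomial outcomes, 250 women per arm, six visits and correlation 0.2. A z-test on woman-level means was counted as protective below −1.96 (nominal 2.5%).

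| c | r = 1.25: RR, protective | r = 1.5: RR, protective | r = 2.0: RR, protective |
|---|---|---|---|
| 30% | 0.85, 20% | 0.74, 47% | 0.59, 86% |
| 50% | 0.89, 16% | 0.80, 40% | 0.67, 82% |
| 70% | 0.93, 10% | 0.87, 22% | 0.77, 58% |

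With r = 1 (no selection) the protective rate was 2.8-3.4%. The intent-to-treat test on the same data rejected in 4.5-5.7% of trials, two-sided, throughout.

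**Ratio that mimics the design effect.** Setting RR = 0.75 gives r = (1/0.75 − c)/(1 − c), which is 1.48, 1.67 and 2.11 for c = 30%, 50% and 70%.

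**Opposite direction.** If compliers are at higher risk, r is below 1. With c = 0.5 and r = 0.8, RR = 1/(0.5 + 0.4) = 1.11, an apparent harm with no product effect.

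**The case against.** **Intent-to-treat comes first and the contrast carries no stated test.** True. C.2.1.1 attaches no alpha or success claim to the secondary comparison, so the rejection rates describe what would follow if it were tested in the usual way. This limits the priority. It does not make the contrast interpretable.

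**An analysis plan may define compliance or add adjustment.** It may, and 12.7 points that way for the main trial. A definition of compliance would leave the one-sided selection in place, and the contrast fixed here has no adjustment.

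**A reader might infer that the error must favour the product.** The documents do not support that. Compliers could use condoms less (12.7.4 plans to study the products' effect on condom use), which could push the other way. The table shows what follows from its premise; it is not evidence that the premise holds.

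**A reader might infer that BV itself ends compliance**, since 9.8 says "In certain cases of infections or epithelial lesions, the study clinician may decide to interrupt diaphragm and gel use". This route is weak. Section 11.2 allows women with a vaginal infection to go on using the products, C.2.2.1 assumes that more than 80% of BV has no symptoms, and C.1 says Gram stains cannot be read in real time. Clinicians would not know of most endpoint events. The point stands without this route.

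**A complier-average estimate looks like the natural replacement**, because control women are "told that they can receive a diaphragm to keep and use as they wish at the end of their participation in the study". Dividing the intent-to-treat difference by the compliant proportion, however, assumes no effect in partial users. Section 8.5 records use on a four-level scale. If half the women comply fully with effect d and the rest get half of it, the intent-to-treat difference is 0.5d + 0.25d = 0.75d, and dividing by 0.5 gives 1.5d, an overstatement of 50%. The estimate also assumes that assignment acts only through product use, which is doubtful when women know their arm and the diaphragm arm receives extra counselling (8.3).

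**Conclusion.** The point holds as a fault in the choice of contrast. C.2.1.1 selects on behaviour after randomisation in one arm only, and nothing in the BV appendix corrects for it. A modest difference is enough to matter: with half the arm compliant, a ratio of 1.25 lifts the chance of a false protective finding from a nominal 2.5% to about 16%, and a ratio of about 1.7 reproduces the whole design effect. These sizes rest on the assumed compliant share and BV ratio and on the assumed direction, none of which the documents give. It would be wrong to infer that the sub-study's primary BV result is compromised, because the intent-to-treat comparison keeps its error rate. The priority is low to moderate.

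**What to change.** In Appendix 16.1, C.2.1.1:
- Keep intent-to-treat as the only inferential comparison for Aim 1.
- Label the compliers-versus-controls contrast exploratory and descriptive, with no p-value and no claim of effect.
- Adjust it for enrolment Nugent status and other baseline characteristics. The enrolment swab (C.1) and the screening and baseline questionnaires (9.3, 9.4) already supply them. The hygiene questionnaire in C.1 is taken at follow-up visits, so its answers arise after randomisation and should not be treated as baseline covariates.
- Show enrolment BV prevalence for compliers, non-compliers and controls side by side, so that the reader can see how far the groups differed before any product use.
- Do not make the intent-to-treat difference divided by the compliant proportion the main complier result. If it is wanted, give it as a sensitivity analysis that states both assumptions: no effect in partial users, and no effect of assignment except through product use.

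The cost is a change of wording in one sub-study, with no new data, visits or participants. The downside is that the secondary contrast can no longer support a claim of efficacy, and adjustment will reduce confounding but cannot be shown to remove it.
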